## 2.2. Hypothesis and Aim

**Aims.** 1. To investigate in a double blind randomized controlled trial in children undergoing open heart surgery if NO exposure during CPB reduces the postoperative duration of invasive mechanical ventilation (defined as ventilator free days within 28 days post randomisation) compared to control.

2. To demonstrate that NO reduces the incidence of low cardiac output syndrome (LCOS), requirement for extracorporeal life support (ECLS), and 28-day mortality

2. To demonstrate that NO reduces the length of PICU stay and health care costs

3. To demonstrate that NO reduces the inflammatory response following CPB.

**Hypotheses.** Infants and children undergoing cardiac surgery on CPB exposed to gaseous nitric oxide (NO) have compared to controls, less myocardial injury and a reduced inflammatory response, leading to reduced incidence of LCOS. We hypothesize that lower LCOS will translate into reduced secondary organ failure and a reduced postoperative intensive care resource utilisation measured by length of mechanical ventilation, and will ultimately result in a reduction in mortality and health care costs.

## 3 STUDY OUTCOMES

### 3.1 Primary outcome

**Length of mechanical ventilation** as defined as the duration of respiratory support for all episodes with an endotracheal tube in situ for the first 28 days post randomisation. The outcome will be reported using ventilator free days (VFD). A systematically zero value will be assigned for patients who die to allow important weight to death as the most pejorative outcome.

### 3.2 SECONDARY OUTCOMES

- Incidence of LCOS, need for ECLS, and Mortality (AIM 2)
- The length of stay in PICU, hospital length of stay and health care costs (AIM 3)
- Levels of systemic inflammatory markers and levels of markers of myocardial injury (AIM 4)

### 3.3 Pre-planned secondary analyses:

- Risk adjustment for preoperative surgical risk (RACHS and Aristotle)
- Health care costs
- Subgroup analysis for age (<28d, <42d, <90d), and univentricular or biventricular hearts
- Number and duration of postoperative organ dysfunction (assessed by respiratory, cardiovascular, renal support)

- Postoperative renal failure, maximum creatinine, need and duration of renal replacement (CVVHF, CVVHDF, peritoneal dialysis, SCUF if on ECLS postoperatively), and blood, serum and urine markers of renal dysfunction including secretory/concentration capacity
- Volume and type of fluid and of transfusions given during CPB, and during the first 24 and 48 hours post CPB in PICU.
- To compare treatment response between patients depending on pre-intervention severity assessed by markers of inflammation and organ failure
- To biochemically define responders to the intervention using markers of inflammation
- Impact of open chest
- To investigate predictors of worse outcome including transcriptomic analyses, biomarkers, and clinical factors
- To investigate the association of hyperoxia with outcomes
- Subgroup analyses on infants and children undergoing several CPB procedures during first years of life, including neurocognitive and functional outcome
- Neurodevelopmental and functional follow-up
- Incidence and severity of postoperative delirium (using sedation and delirium scoring)
- Relationship of postoperative delirium and neurodevelopmental outcomes to intervention and inflammation

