## **6 INTERVENTION**

## 6.1 Treatment arms

Patients allocated to the study gas arm will receive NO, which will be blended into the fresh gas flow kept at 3L/min for the CPB oxygenator with NO levels maintained at 20 ppm via an Ikaria INOmax DSIR (Ikaria, NJ, USA) or similar device. Continuous sampling of NO and NO2 concentration will be undertaken from an access port just prior to the oxygenator. NO will be started immediately when the patient is on CPB and ceased once coming off CPB at the completion of MUFing. Patients allocated to the Placebo arm will receive standard respiratory gases (oxygen-air mix) during bypass at a flow rate of 3L/min. Partial pressures of CO2 will be maintained constantly in both study arms as per the institutional practice.

*Note:* If patients require several CPB runs during the same procedure, the treatment has to be provided for each run using the same treatment allocation for every run (i.e. patients allocated to study gas arm will receive NO at 20ppm for every run).

**Subsequent CPB procedures:** Patients that were previously enrolled and randomised into the study with surgical procedure performed that required use of cardio-pulmonary bypass will not get re-randomised. Previously enrolled and randomised patients will undergo the same treatment allocation for subsequent surgeries, unless parents opt out. The study perfusionists at each study site have access to the treatment allocation, which will remain blinded for all other study team members.

**Blinding arrangements.** Of the investigating team, only the study perfusionist will be aware of the randomisation and NO delivery. Blinding arrangements in the operating theatre will be achieved by covering the NO delivery system with drapes. The dedicated study NO delivery system will be connected to the CPB oxygenator at all times, independent of randomisation. The surgeons, anaesthetists and ICU staff will be not aware which treatment arm a patient been allocated to. The perfusionists will be advised that all aspects of CPB except for provision of NO (or not) should be performed in a standard fashion for study participants. The perfusionist does not attend the surgical handover in PICU. The Data Safety Monitoring Board will be unblinded in the event of a severe adverse event. In our pilot study and the previous published study by Checcia, methaemoglobin values using NO at 20 ppm were similar in both the control and intervention groups (1.4%) [29].

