### 7.3 Blood Sample Collection for Inflammation analysis

**Biomarker Analysis and Biobanking:** Blood markers for myocardial injury and inflammatory response will be collected on induction of anaesthetics (baseline – pre bypass), at admission to PICU (0 hours – post bypass) and at 12, and 24 hours for the following purposes: i) to test the impact of the intervention on markers of inflammation; ii) to stratify patients in to high- versus low inflammatory groups; iii) to biochemically define responders to the intervention (to identify patient subgroups that are more likely to respond to a specific treatment), iv) to develop improved markers of outcome post cardiac surgery. Collection of blood for biomarker analysis and biobanking is optional and parents will be asked to provide their permission during the consenting process.

**Blood sampling and processing.** *Preoperative baseline* (before onset of cardiac surgery, done by anaesthetist during the induction of the patient once the arterial line has been inserted): 1-2ml of EDTA blood (for DNA), 2.5ml of blood (PAXgene tube for gene expression markers), 1-2ml of serum *Postoperative at 0,12,24 hrs* (in PICU until discharge to the ward): 2.5ml of blood (PAXgene tube - time point 0 only), 1-2ml of serum. The total amount of blood taken is 10-15ml for the entire study duration, which is much less than the amount of blood taken for routine perioperative care tests. The samples will be processed within 30 minutes, centrifuged, aliquotted and immediately frozen. The samples will be kept in a security protected freezer in the each institution, and will be transferred in batch every 12 months to the Centre for Children's Health Research, Brisbane, Australia. Urinary electrolytes and NH4 will be measured from patient urine collected through the

standard IDC at baseline, admission to PICU, and 6-24hours to assess for renal concentration and secretory function. Paired arterial and venous gases will be collected postoperatively at 0,6,12,24,48 hrs (in PICU until discharge to the ward or removal of arterial line, whichever occurs first) to assess for lactate and SaO2-SvO2 gradient. Each arterial or venous blood gas sample requires 0.2mls of blood and would total 2mls across all samples. Routine paired gases are often part of standard clinical care.

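### Section 7.3 plans high/low inflammation groups with no cut-point and no named sample; treatment-response analyses should use the pre-bypass marker, kept continuous

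*Combined protocol and SAP*

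**What the plan says.** Protocol section 3.3 lists, among the pre-planned secondary analyses, "To compare treatment response between patients depending on pre-intervention severity assessed by markers of inflammation and organ failure". It names no marker, functional form or model and does not refer to section 7.3. A separate item in the same list is to define responders biochemically from inflammation markers; that item carries no pre-intervention limit.

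Section 7.3 lists one sample at induction, before bypass, and then three more: "at admission to PICU (0 hours – post bypass) and at 12, and 24 hours for the following purposes". One list of four purposes follows. Purpose (i) is the effect of NO on the markers. Purpose (ii) is "to stratify patients in to high- versus low inflammatory groups". Purpose (iii) is to define responders and find subgroups more likely to respond. Purpose (iv) is better outcome markers. No sentence ties a purpose to a time point, and no cut-point is given.

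On exposure, section 6.1 states: "NO will be started immediately when the patient is on CPB and ceased once coming off CPB at the completion of MUFing". Section 2.2 includes the aim "To demonstrate that NO reduces the inflammatory response following CPB". On numbers, section 7.3 adds: "Collection of blood for biomarker analysis and biobanking is optional".

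The SAP does not settle the matter. Its statistical analysis principles leave inflammatory markers to separate reporting, and its subgroup section covers age and physiology only.

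**The concern.** Two weaknesses meet in one analysis. First, the only grouping described cuts a continuous marker in two, which weakens any test of whether the NO effect varies with inflammation. Second, three of the four listed samples follow NO exposure. A child's place in a high or low group formed from them could itself be a result of treatment, so the arms within a group would no longer be the comparison that randomisation created. Part of any benefit that acts through inflammation would also be conditioned away.

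At stake is the trial's answer to which children benefit. A real gradient could be missed, or NO could look weaker than it is in both groups. With marker, time point and cut-point all open, they could also be chosen after the results are seen.

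**Working it through.** **The plan's own figure.** Sections 11.2 (protocol) and Sample size (SAP) give 1320 for ventilator-free days, from 0.2 SD, 90% power and two-sided 5%. Per arm, 2 × (1.960 + 1.282)² / 0.2² = 525.4, so 526. Applying the 15% and 10% allowances gives 1316 (526 × 1.25 = 658 per arm), 1332 (526 × 1.15 × 1.10 = 666) or 1346 (526 × 1.15 / 0.9 = 673). The stated figure reproduces to within 3%. Neither document states power for the inflammation-modifier analysis.

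**Step 1: cost of the split.** Assume a normal marker (after logging if skewed), 1:1 allocation, residual SD 1 and a linear gradient. The information kept by a cut at quantile q is φ(z_q)² / [q(1 − q)].

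- Median: 0.3989² / 0.25 = 0.637, so 36% is lost and 1 / 0.637 = 1.57 times the children are needed.
- 75th centile: 0.539 kept, 1.86 times.
- 90th centile: 0.342 kept, 2.92 times.

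If the continuous marker gives 90% power, the signal is 1.960 + 1.282 = 3.242 standard errors. At a median split it is 3.242 × √0.637 = 2.587, and power is Φ(2.587 − 1.960) = 73%. The other two cuts give 66% and 48%. Starting from 80%, a median split gives 61%.

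For an interaction of g SD of outcome per SD of marker, power = Φ(g√(N × information kept) / 2 − 1.960). Both g and the number sampled are assumptions. The table shows continuous versus median split, in per cent.

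| Children sampled | g = 0.1 | g = 0.2 | g = 0.3 |
|---|---|---|---|
| 400 | 16.9 v 12.3 | 51.6 v 35.8 | 85.1 v 66.8 |
| 660 | 25.0 v 17.5 | 72.9 v 53.6 | 97.1 v 86.8 |
| 924 | 33.0 v 22.7 | 86.0 v 67.9 | 99.5 v 95.3 |
| 1188 | 40.6 v 27.9 | 93.1 v 78.5 | 99.9 v 98.5 |

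**Step 2: which samples follow NO.** NO runs only during bypass, so the 0, 12 and 24 h samples all follow exposure and only the induction sample precedes it.

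**Step 3: size of the attenuation if a post-bypass sample were used.** Suppose NO lowers the marker by 0.5 SD. The pooled median lies at −0.25 on the control scale. The high group then holds Φ(−0.25) = 40% of NO children and Φ(0.25) = 60% of controls. Mean marker in that group is 0.3867 / 0.5987 = 0.646 for controls and −0.5 + 0.3867 / 0.4013 = 0.464 for NO. The arms differ by 0.182, which is 36% of 0.5. By symmetry the low group gives the same.

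A fully mediated effect therefore shrinks to about 36–37% of its size, and a half-mediated one to 0.5 + 0.5 × 0.365 = 68%. A simulation of 2,000,000 children per scenario (baseline-to-post correlation 0.5; NO effect on the marker 0.3, 0.5 or 0.8 SD) agrees. The table gives the within-group effect as a share of the overall effect.

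| Share of benefit acting through marker | Baseline split | Post-bypass split | Post-bypass split, unmeasured cause of marker and outcome |
|---|---|---|---|
| None | 100% | 100% | 91–77% |
| Half | 100% | 68% | 60–45% |
| All | 100% | 37% | 28–14% |

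**The case against.** The strongest reply is that section 3.3 already fixes the timing. It says pre-intervention, and the induction sample exists to serve it. Purpose (i) alone explains the post-bypass samples, and section 7.3 shows that not every tube is drawn at every time. A reader might infer that the protocol plans to group children on samples taken after NO. It does not say so: the fault is an unresolved ambiguity between two sections. The ambiguity remains, because serum is drawn at all four times, the cytokines are to be measured in serum, and purpose (iii) and its counterpart in 3.3 have no timing limit.

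A reader might also infer that the treatment-response analysis is committed to high/low groups. Section 3.3 does not say that, and linking it to purpose (ii) is an inference. What can be said is that no other grouping by inflammation is described.

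Third, the model is deferred rather than wrongly chosen. The SAP treats secondary and other results as exploratory, reported with intervals, so the power of a 5% test carries less weight. That is fair, but the loss also affects precision: relative to the effect, the standard error grows by √1.57 = 1.25.

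Fourth, the figures are illustrative. With g = 0.1 the continuous analysis is weak too, and the fix does not rescue it. Ventilator-free days are bounded, set to zero for deaths and analysed by rank and quantile methods, so the percentages do not transfer directly. Both points stand.

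**Conclusion.** The point holds in a limited form. Section 7.3 describes a high/low grouping with no cut-point and no restriction to the pre-NO sample, and nothing in the SAP replaces it. If that grouping is used for the section 3.3 question, a median split discards about 36% of the information and turns 90% power into about 73%, assuming a normal marker and a linear gradient.

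A reader might conclude that the plan will hide the NO effect. The documents do not support that. Attenuation arises only if post-bypass samples are used, and its size depends on mediation and on unmeasured common causes. The 37% figure is the full-mediation case without such a cause. Some mediation is the trial's own hypothesis, but its share, the marker's correlations and the number of children sampled are not in the documents.

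The primary intention-to-treat result and the 1320 are untouched. This is a free improvement to a secondary, exploratory analysis.

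**What to change.** In section 3.3, and in purposes (ii) and (iii) of section 7.3, state that treatment-response (effect-modification) analyses use the induction, pre-bypass sample only.

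Enter the marker as a continuous variable, logged if skewed, with an arm-by-marker interaction in the adjusted outcome model. The SAP already uses an interaction term for its age and physiology subgroups, so this extends its own method. Show high/low groups as illustration only, at a cut-point fixed in advance. Analyse the 0, 12 and 24 h values as outcomes or mediators, not as definitions of subgroups.

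The cost is wording: the same samples and the same assays. Section 7.3 says cytokines are measured together at the end of the study, so the definition can be fixed before those results exist.

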## 4 STUDY DESIGN

### 4.1 Type of Study

A multi-centre randomised controlled and blinded study in children < 2 years of age undergoing open heart surgery on cardiopulmonary bypass.

[figure not shown]

**Figure 1. Study Flow Diagram:**

## 4.2 Study Setting

Cardiac and Paediatric Intensive Care Services of Royal Children's Hospital, Melbourne; Starship Children's Hospital Auckland NZ; Queensland Children's Hospital Brisbane; Westmead Children's Hospital, Sydney; Princess Margaret Children's Hospital, Perth; and Utrecht Medical Center, Utrecht, Netherlands.

## 5 PARTICIPANTS, RECRUITMENT AND CONSENT

### 5.1 Eligibility Criteria

#### 5.1.1 Inclusion criteria

- All infants and children < 2 years of age undergoing open heart surgery on CPB
- Elective cardiac surgery and consent of parents/guardian.

#### 5.1.2 Exclusion criteria

- Signs of persistently elevated pulmonary vascular resistance preoperatively requiring iNO or preoperative intravenous use of drugs involved in the NO pathway such as GTN, within 48 hours prior to CPB (oral sildenafil treatment alone is not an exclusion).
- Patient is on ECLS immediately prior to surgery

- Chronic ventilator dependency
- Concurrent known confirmed bacterial sepsis/septic shock, diagnosed within <48 hours prior to surgery and being actively treated with antibiotics at time of surgery (suspected sepsis treated with antibiotics is not an exclusion criteria unless inotropes are required for treatment of septic shock at time of surgery)
- Preoperative acute respiratory distress syndrome requiring HFOV ventilation <48 hours of surgery
- Patient requires high doses of vasoactive drugs prior to surgery with an inotrope score  $\geq 15$  met within 24 hours prior to surgery: Inotrope requirement will be calculated by means of the Vasoactive-Inotrope Score (VIS) (2):  $VIS = \text{dopamine dose (mcg/kg/min)} + \text{dobutamine dose (mcg/kg/min)} + 100 \times \text{adrenaline dose (mcg/kg/min)} + 100 \times \text{noradrenaline dose (mcg/kg/min)} + 10 \times \text{milrinone dose (mcg/kg/min)} + 10,000 \times \text{vasopressin dose (U/kg/min)}$ .
- Cardiac arrest within one week (7d) prior to surgery
- Emergency cardiac surgery which may preclude obtaining informed consent (defined as acutely required life-saving procedure in a patient unlikely to survive the next hours without the surgery)
- Pre-existing methaemoglobinemia (MetHb > 3%)

NB. Patients that were previously enrolled and randomised into the study with surgical procedure performed that required use of cardio-pulmonary bypass will not get re-randomised. Previously enrolled and randomised patients will undergo the same treatment allocation for subsequent surgeries, unless parents opt out. Rationale: For patients undergoing same procedures, any potentially additive protective impact of NO during CPB on long-term neurodevelopment may become diluted by use of CPB without NO during subsequent procedures. We expect that ca. 10% of all CPB cases <2 years may require subsequent CPB <2 years of age.

## 5.2 Recruitment and identification of potential participants

Only parents/guardians of elective cardiac surgical children will be approached for consent. Consent will be obtained from parents/guardian prior to surgery either in pre admission clinic or whilst the patient is in hospital prior to surgery. A screening log will be maintained to document missing patients.

## 5.3 Consent

Consent will be sought from the parents of every child <2 years of age undergoing CPB for elective cardiac surgery over the study period. When the family is seen by the surgeons in pre-assessment clinic (usually days prior to surgery), the study will be mentioned to them by the surgeon. In addition, the study team will provide study information prior to hospitalization to families, including printed study flyers, and links to online study documentation (media release). A video detailing the study has also been prepared and is available to families. These will not replace consent, but support the consent process inasmuch as parents will have more time and more information available to

consider prior to consenting. Pre-admission contact can be made by phone, too, if not feasible directly. While parents may provide verbal consent, written consent will have to be obtained no later than the day of surgery in such circumstances.

The study team will meet the family and they will be given the study Information Statement and the consent form if they are interested. When the patient and family return to hospital for the operation, further explanation will be offered by a member of the research team and consent taken if the family wish to take part in the study. All endeavours will be made to consent parents by face-to-face meetings prior to the day of surgery, however due to the changing nature of that cardiac surgical bookings parents may be approached on the morning of surgery. Early phone contact with parents not present at the hospital or not attending pre-surgical clinics will be made. If parents give consent by phone it will be later confirmed by written consent during hospital/PICU stay.

The consent form will make it clear that standard medical treatment of children will be unaffected by participation in the study. Taking part is voluntary and will be free from coercion.

The research team will be available to field any questions from the parents prior to the consent form being signed.

The following basic principles of obtaining consent will be followed: Explain the project to the child's family in language that they understand. Generally, consent should be obtained in privacy and parents given as much time as possible to consider the study before consent.

It is important that the investigator considers the parent/guardian(s) has a good understanding of what the study means for their child before they sign the consent form. If the parent/guardian(s) is unable to give informed consent, their child should not be recruited into the study. It should also be made clear that the parent/guardian(s) is free to not have their child participate in the study and that if they do so, their medical care within the hospital will not be affected in any way. In addition, the parent/guardian(s) of the child should be informed that the data collected about themselves and their child will be de-identified before publication and their child's name will not appear on any publications that may arise from the trial.

Patients that were previously enrolled and randomised into the study with surgical procedure performed that required use of cardio-pulmonary bypass will undergo the same treatment allocation for subsequent surgeries requiring bypass, unless parents opt out.

#### **Phone consent during the COVID-19 pandemic**

COVID-19 restrictions within healthcare facilities affected the recruitment process of study patients, approval was obtained to contact families via telephone when we are not able to contact as per normal routine. The patient cohort are not affected directly by COVID-19, as they are pre surgical patients and at little risk of being COVID-19 positive.

COVID-19 restriction on research/parental experience:

- Hospital health checks on arrival (temp, wellness)
- Parental/ Guardian support reduced with visitor restrictions
- Research staff restricted from high risk areas
- Research staff working from home

Verbal consent allows the study nurses to contact families who are interested in participating in the study after speaking to the cardiac surgeons. This allows families to consider research in the comfort of their own homes with no pressure of the admission and COVID-19 restrictions within the hospital. If they wish to participate, the research nurse will take verbal consent over the phone. Research will always aim to retrieve consent in the normal manner whenever possible. We would resume standard practise as soon as outpatient clinic returns to normal.

